**Table Taba:** 

Service provided	Control group	Intervention group
Baseline laboratory values (creatinine, CD4-count, haemoglobin)	Blood taken at first clinic visit after the positive HIV test result, results communicated at second clinic visit.	Performed in the community the day of the HIV test result as point-of-care
Adherence-counselling	At first and second clinic visit	In the community, directly after the HIV test result
ART-initiation	After at least two adherence counselling sessions at the clinic	Proposition of starting the same day as tested HIV positive
Follow-up visits and drug-refills at the clinic	Monthly	2 weeks – 6 weeks – 3–6–9–12 months

Table 1 Overview of services provided after a positive HIV test result during community-based HTC campaigns in the control and intervention group

**Fig. 1 Fig1:**
[figure not shown]
CONSORT flow-chart of the CASCADE-trial. HTC: HIV testing and counselling; ART: anti-retroviral therapy

### Primary outcomes

The trial has two primary outcomes. The first primary outcome is linkage to care within 3 months after having been tested HIV positive during the HTC-campaign. A patient is considered to have linked to care if he/she attends the clinic at least once within 90 days after enrolment in the trial. The second primary outcome is viral suppression 12 months after enrolment in the trial. Viral suppression is defined as a viral load (VL) <100 copies/mL between 11 and 14 months after diagnosis of HIV-infection.

### Secondary outcomes

Secondary outcomes are defined in Table 1.

**Table 1 Tab1:** Secondary outcomes

Secondary outcome	Definition	Time-frame	Remarks
ART-initiation	Participant started ART	3 months after the enrolment	
1-year retention in care	Proportion confirmed dead (death record at clinic or confirmed by a first-grade relative), lost to follow-up (not attending the clinic 11–14 months after HIV-test and not confirmed dead), and retained in care (on ART, attends the clinic)	12 months (11–14 months) after enrolment	Participants with transfer out to another clinic are excluded from analysis. Participants are considered as transferred out if the facility where they were enrolled in care issued a transfer letter.
Viral suppression under ART	VL<100 copies/mL among those who started ART	6 months (5–7) months) after ART initiation	
Change in body weight	Delta between body weight (kg) at baseline and 12 months after enrolment	At baseline and 12 months (11–14 months) after enrolment	
Change in CD4 cell count	Delta between CD4 cell count (cells/mL) at baseline and 12 months after enrolment	At baseline and 12 months (11–14 months) after enrolment	
Change in haemoglobin	Delta haemoglobin (g/dL) at baseline and 12 months after enrolment	At baseline and 12 months (11–14 months) after enrolment	
New clinical WHO stage 3 or 4 events	Diagnosis of a new clinical WHO stage 3 or 4 event confirmed by study-physician	12 months (11–14 months) after enrolment in the trial	WHO 3 or 4 events occurring within 3 months after ART-initiation and judged as immune reconstitution inflammatory syndrome by the study physician will not be classified as a new WHO stage 3 or 4 event

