## Methods

### Trial design

The CASCADE-trial is a two-armed open-label randomized controlled trial. Allocation is 1:1 with parallel assignment. The intervention is targeted to individuals who tested HIV-positive during community-based HTC and entails same day community-based ART start combined with less frequent follow-up visits. The intervention arm will be compared to the standard of care in Lesotho (referral to facility for ART initiation followed by monthly follow-up visits). The primary outcomes are linkage to care at 3 months and viral suppression at 12 months after a positive HIV test.

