Participants randomized to the intervention group receive post-test counselling and clinical and laboratory assessment with the possibility of same day ART start combined with a reduced frequency of follow-up visits. Directly after the positive HIV-test result the study nurse assesses the participant clinically and performs point-of-care laboratory testing (serum creatinine (StatSensor Creat®, Nova® Biomedical), haemoglobin (Hemocue®, HB301), and CD4 cell-count (PIMA Alere®)). Thereafter, the participant receives a standardized short adherence counselling. After adherence counselling, if – according to the nurse’s judgement - the person understood the implications of lifelong ART, he/she will be offered to start ART immediately. Those who decide to start ART during the visit or intend to start within 7 days will receive a 30-day ART-supply and a follow-up appointment at the clinic within 12 to 16 days. Choice of ART regimen and use of cotrimoxazole prophylaxis follows national and international guidelines [36, 37]. Participants with a CD4 cell-count < 100 cells/mL will receive testing for cryptococcal antigen. In case of a positive result, the participant will be treated according to guidelines and excluded from the study. In order to reduce travel time and transport cost, participants who are clinically stable, will have their follow-up visits and ART refills more widely spaced with appointments at 6 weeks, 3, 6, (9) and 12 months after ART initiation. Participants are, however, encouraged to visit the clinic at any time in case of problems or questions.

Figure 1 summarizes flow of participants in the study.

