### Sample size and randomization

Households will be randomly allocated to a study arm at a ratio of 1:1. A randomization list was generated by an independent statistician with a block size of 4. Sealed and consecutively numbered envelopes containing treatment assignment and study documents are provided to the study nurses. It was not possible for treatment to be blinded.

The sample size for this trial is based on the primary endpoint of linkage to care within 3 months after HIV diagnosis. We expect 3-month linkage to care rates of 40 % in the control and 60 % in the intervention arm. As the trial is randomized at the household level, we require a total of 260 households with at least one HIV-positive participant to detect a 20 % increase in linkage to care assuming a Type I error rate of 5 % and power of 90 %. With an estimated uptake of HTC of 94 %, a prevalence of previously untreated HIV infection during home-based HTC campaigns of 5 %, and a 10 % trial participation refusal rate or choice of alternative health facility, we need to visit 6200 households to achieve the desired sample size of 260 households. In case more than one HIV-positive individual is diagnosed in the household, all individuals meeting eligibility criteria will be included and randomized to the same arm. This will only serve to increase the power of the study.

With the proposed sample size above, we will have sufficient power to test the second primary endpoint of viral suppression at 12 months. As those not linking to care will be considered as failures, we expect viral suppression rates of 25 % in the control arm and 45 % in the intervention arm. With 130 individuals per arm, we will have 93 % power to detect a difference of 20 % in viral suppression rates.

Analysis will be as intention to treat. The study will be analysed using mixed effects logistic regression models in order to account for the clustering of households (if sufficient number of households include more than one HIV-positive individual in the study) and village. If the arms are not found to be balanced on important risk factors for linkage to care and viral suppression, these risk factors will be adjusted for in models. Linkage and viral suppression rates between the control and intervention arm will be presented with odds ratios and 95 % confidence intervals.

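### The stage 3/4 event outcome drops events by a rule tied to ART start, which the intervention changes, so the exclusion can fall unequally on the arms

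*Protocol article*

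**What the plan says.** In the table under Secondary outcomes, the event is defined as "Diagnosis of a new clinical WHO stage 3 or 4 event confirmed by study-physician", with the time frame "12 months (11–14 months) after enrolment in the trial". The remarks column then takes some events out: those in the first 3 months of ART "judged as immune reconstitution inflammatory syndrome by the study physician will not be classified as a new WHO stage 3 or 4 event". The outcome clock runs from enrolment and the exclusion clock from ART initiation. The same study-physician role confirms the event and makes the judgement that removes it.

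The arms differ by design in when ART can begin. In the intervention arm the service table gives "Proposition of starting the same day as tested HIV positive", and Control and intervention arms says that after counselling a participant who has understood what lifelong ART implies "he/she will be offered to start ART immediately". In the control arm ART follows at least two counselling sessions at the clinic. Sample size and randomization states an intention-to-treat analysis and says of masking: "It was not possible for treatment to be blinded".

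**The concern.** An event can be removed only if ART has already started. A stage 3 or 4 illness in month 2 stays in the count for a control participant not yet on ART, provided it is diagnosed and confirmed. In an intervention participant who started on the day of the test, the same illness may be removed. Whether an event counts thus depends on something that happens after randomisation and that the intervention alters. This fits poorly with an intention-to-treat comparison: if earlier or more frequent ART start brings immune reconstitution illness with it, that illness is part of the effect of the strategy, and the rule subtracts it.

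This is the only event-based morbidity outcome among those listed. The others are linkage, ART start, retention, viral suppression, weight, CD4 count and haemoglobin. Deaths appear only within retention, and no listed outcome counts the removed events.

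**Working it through.** **Figures available.** The article gives no event rate, immune reconstitution rate or sample size for this outcome, so there is no stated figure for it to reproduce. The group size used below does reproduce: for 40% and 60% linkage, two-sided 5% error and 90% power, n = [1.960·√(2·0.5·0.5) + 1.282·√(0.4·0.6 + 0.6·0.4)]² / 0.20² = (1.386 + 0.888)² / 0.04 = 129.3. That is 130 per arm and 260 in total, as stated.

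**Step 1: share of removals by arm.** Let a be the proportion starting ART in an arm, and q the risk per ART starter of an event that is removed, taken as equal in both arms. Removals per arm are 130·a·q, so the intervention share is a_I / (a_I + a_C) and does not depend on q. No rate of ART start is given, so proxies are needed:
- expected 3-month linkage, 60% and 40%: 0.60/1.00 = 60%
- expected 12-month suppression, 45% and 25%: 0.45/0.70 = 64%
- assumed 80% and 40%: 0.80/1.20 = 67%
- assumed near-equal uptake, 70% and 60%: 0.70/1.30 = 54%
- equal uptake: 50%

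The 80%/40% row is shown because an intervention participant can start ART at home without attending the clinic, while a linked control has not necessarily started.

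**Step 2: numbers of events.** With the 60%/40% proxy and q assumed at 3%, 5% and 10%:

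| q | Removed, intervention | Removed, control | Net difference | Risk difference left out |
|---|---|---|---|---|
| 3% | 130·0.6·0.03 = 2.3 | 130·0.4·0.03 = 1.6 | 0.8 | 0.6 points |
| 5% | 3.9 | 2.6 | 1.3 | 1.0 point |
| 10% | 7.8 | 5.2 | 2.6 | 2.0 points |

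At 80%/40% and q = 10% the net difference is 10.4 − 5.2 = 5.2 events, or 4 points. With an assumed background risk of 5% or 10%, power to detect differences across this whole range is about 4% to 18%.

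**Step 3: effect on the risk ratio.** Suppose true event risks are equal. Let w be the share of an arm's events inside the 3-month window and s the share of those labelled immune reconstitution. The reported ratio is (1 − w_I·s) / (1 − w_C·s). Setting w to 0.60 and 0.40, which treats every event among linkers as falling in the window, and assuming s:
- s = 20%: 0.88/0.92 = 0.96
- s = 40%: 0.76/0.84 = 0.90
- s = 60%: 0.64/0.76 = 0.84

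**Step 4: an opposing force.** An event counts only if it is diagnosed and confirmed. If detection tracked linkage (an assumption), equal true risks would give a detection ratio of 0.60/0.40 = 1.5. Multiplying by the factors in step 3 gives 1.5 × 0.88/0.92 = 1.43 to 1.5 × 0.64/0.76 = 1.26. If only linkers' events were recorded, the removal factor would itself move towards 1 and the product towards 1.5. Either way the recorded ratio would exceed 1. Less frequent intervention visits could push the other way.

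**The case against.** The strongest defence is that the rule is prespecified, has a fixed window and is worded identically for both arms. Controls who start ART later get the same 3-month window within the 12 months, and everyone stays in the denominator. Separating immune reconstitution reactions from new disease progression is a coherent aim for an outcome called new events. The entry criteria exclude WHO stage 4 disease, active tuberculosis and a positive cryptococcal antigen test, which should make such reactions less frequent. The outcome is one of seven secondary outcomes, with little power, and neither primary outcome is touched.

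All of this limits the size of the problem. None of it removes the dependence on ART start: an identical rule applied to a variable that differs by arm still acts unequally, and the separation can be shown in a table without deleting events from the comparison.

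A reader might go further and infer that an unblinded physician strips events mainly from the same-day arm and so conceals a harm. The documents do not support that. On their own expected rates the intervention share is 60% to 64%, a majority but not a near-monopoly. The article says the trial is open-label; it does not say whether the classifying physician sees allocation. Step 4 shows that incomplete detection in unlinked controls could reverse the net direction. The article is condensed, and the full protocol may record immune reconstitution as safety data.

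**Conclusion.** The point holds as a defect in how the outcome is defined: the exclusion is conditioned on a post-randomisation variable that the intervention changes, and it can understate morbidity under same-day ART. The 60% to 64% share rests on linkage or suppression standing in for ART start, and on equal risk of a removed event per starter; it falls to 50% if uptake is equal, which is contrary to the trial's premise. The apparent risk ratio of 0.96 to 0.84 under no true difference rests further on the assumed 20% to 60% labelling share and on all linkers' events falling in the window. Absolute numbers are probably small, and the net direction after allowing for detection is not known. The point deserves correction because this is the only listed comparison of new illness for a strategy proposed for scale-up.

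**What to change.** Change the remark in the secondary-outcomes table so that the main between-arm comparison counts every physician-confirmed new stage 3 or 4 event from enrolment to 12 months. Tabulate the events judged to be immune reconstitution separately by arm, and keep the present exclusion as a sensitivity analysis. Where feasible, have the classification made from records that do not show allocation. The ART start date cannot be withheld, because the window is counted from it, and it may reveal the arm, so masking will be partial.

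The cost is one sentence and one extra table, using events that the study physician already has to review. The downside is that the intervention arm's count may look less favourable. The change does not cure under-detection in participants who never attend, which should be stated as a limitation when the comparison is reported.

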### Sample size and randomization

Households will be randomly allocated to a study arm at a ratio of 1:1. A randomization list was generated by an independent statistician with a block size of 4. Sealed and consecutively numbered envelopes containing treatment assignment and study documents are provided to the study nurses. It was not possible for treatment to be blinded.

The sample size for this trial is based on the primary endpoint of linkage to care within 3 months after HIV diagnosis. We expect 3-month linkage to care rates of 40 % in the control and 60 % in the intervention arm. As the trial is randomized at the household level, we require a total of 260 households with at least one HIV-positive participant to detect a 20 % increase in linkage to care assuming a Type I error rate of 5 % and power of 90 %. With an estimated uptake of HTC of 94 %, a prevalence of previously untreated HIV infection during home-based HTC campaigns of 5 %, and a 10 % trial participation refusal rate or choice of alternative health facility, we need to visit 6200 households to achieve the desired sample size of 260 households. In case more than one HIV-positive individual is diagnosed in the household, all individuals meeting eligibility criteria will be included and randomized to the same arm. This will only serve to increase the power of the study.

With the proposed sample size above, we will have sufficient power to test the second primary endpoint of viral suppression at 12 months. As those not linking to care will be considered as failures, we expect viral suppression rates of 25 % in the control arm and 45 % in the intervention arm. With 130 individuals per arm, we will have 93 % power to detect a difference of 20 % in viral suppression rates.

Analysis will be as intention to treat. The study will be analysed using mixed effects logistic regression models in order to account for the clustering of households (if sufficient number of households include more than one HIV-positive individual in the study) and village. If the arms are not found to be balanced on important risk factors for linkage to care and viral suppression, these risk factors will be adjusted for in models. Linkage and viral suppression rates between the control and intervention arm will be presented with odds ratios and 95 % confidence intervals.

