### Recruitment and participants

Participants will be recruited during community-based HTC campaigns in the district of Butha-Buthe, in northern Lesotho. Lesotho has an estimated adult HIV-prevalence of 23.4 %. Among the hyper-endemic countries of southern Africa it has the highest transmission rate and the lowest ART coverage [33]. Butha-Buthe is a rural district with an estimated 110,000 habitants, mostly subsidence farmers or mine workers, or construction or domestic workers in neighboring South Africa. The district has only one small town (Buthe-Buthe, ca. 25,000 habitants), the remaining habitants live in villages scattered over a partly mountainous surface of 1,767 km^2^. According to UNAIDS an estimated 11,000 HIV-infected adult persons lived in the district in 2013 [34].

Home-based HTC campaigns will be conducted for an anticipated period of 3 months beginning at the end of February in the catchment areas of six health care facilities - four nurse-led health centers, one missionary and one public hospital.

For rural areas, villages were randomly selected from a list of eligible villages. A village is eligible if it is clearly confined to the catchment area of one of the six facilities and if it comprises between 40 and 80 households. In Butha-Buthe town urban neighbourhoods were randomly selected.

Three teams consisting of 4 lay counsellors, each supervised by one professional counsellor and a nurse visit all households in selected villages and urban neighbourhoods proposing HTC to all household members. Each house will be visited once during the workweek. During this first visit, lay counsellors enquire about absent household members. If a household member is absent, the household will be visited a second time during a weekend. The HTC-coverage in visited areas will be assessed as part of a nested study (see nested studies below).

If a household member tests HIV positive during the HTC campaign, the study nurse is called to assess whether the individual is eligible for the CASCADE trial. Consenting individuals 18 years or older, living or working in the district of Butha-Buthe, having never been on combination ART and willing to receive follow-up at one of the six study facilities are eligible. Exclusion criteria are: pregnant or breast-feeding, already enrolled in care for another chronic disease, clinical WHO stage 4 or active tuberculosis, or a positive cryptococcal antigen test.

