### Ethics

The trial protocol has been approved by the Ethical Board in Switzerland (Ethikkommission Nordwestschweiz; EKNZ UBE 15/123) and the National Health Research and Ethics Committee of the Ministry of Health of Lesotho (89-2015). For the home-based HTC campaigns the head of household or his/her substitute must provide written informed consent to the lay counsellor to visit the household and to propose HTC to household members who are present. As per Lesotho National HTC guidelines each individual who agrees to HIV testing must sign the National HTC Consent Form. In case an individual is eligible for the CASCADE-trial he or she will be asked for written informed consent. Individuals who are not able to sign with their name can provide a thump-print.

Individuals who participate in nested study 2 as HIV-negative controls sign a specific informed consent form for blood draw and analysis of their lipid-status and glycosylated haemoglobin (HbA1c) (see below for nested study 2).

Individual participating in the CASCADE trial or one of the nested studies will not receive any financial compensation.

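### Household members found at the weekend visit can be enrolled with their arm already known, and a single block size of 4 makes some allocations partly predictable

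*Protocol article*

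**What the plan says.** The unit of allocation is the household (Protocol article, Sample size and randomization): "Households will be randomly allocated to a study arm at a ratio of 1:1". Where a household has more than one HIV-positive member, "all individuals meeting eligibility criteria will be included and randomized to the same arm". The section adds that this can only raise power.

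The same section describes how the list was made: "A randomization list was generated by an independent statistician with a block size of 4". No other block size is mentioned. Concealment rests on what the recruiting staff hold: "Sealed and consecutively numbered envelopes containing treatment assignment and study documents are provided to the study nurses". On masking, the section is equally plain: "It was not possible for treatment to be blinded".

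Recruitment and participants sets out two household visits, the first in the working week: "If a household member is absent, the household will be visited a second time during a weekend". When somebody tests positive, "the study nurse is called to assess whether the individual is eligible for the CASCADE trial". The eligibility criteria in that section include readiness to be followed up at a study clinic. Entry also needs individual agreement (Ethics): "In case an individual is eligible for the CASCADE-trial he or she will be asked for written informed consent".

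Under Control and intervention arms, an intervention participant is assessed, counselled and offered treatment on the day of the positive test. A control participant receives counselling and a referral letter.

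**The concern.** Read together, these rules allow recruitment into a household after it has been allocated. The services given to the first positive member reveal the arm to the nurse and probably to the household. A member who tests positive at the weekend visit is then assessed and asked for consent with that knowledge.

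Two entry steps could respond to it. One is the person's own decision: same-day treatment at home with widely spaced visits, or referral with monthly visits. The other is the criterion on willingness to attend a study clinic, which lies close to the first primary outcome, clinic attendance within 90 days. If the people who enter late differ by arm, the comparison of both primary outcomes could be distorted. Intention to treat keeps enrolled people in their arm, but it cannot bring back those who selectively did not enrol. Covariate adjustment covers only measured factors. Saying that extra members can only help power overlooks this.

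A smaller, separate issue concerns the first member of each household. The nurse who judges eligibility also holds the numbered envelopes, and the list uses one small block size in an open-label trial. Knowledge of earlier assignments can therefore inform a guess at the next one.

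**Working it through.** **1. The plan's own figures.** Inputs from Sample size and randomization: linkage 40% v 60%, type I error 5% (taken as two-sided), power 90%.

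n per arm = [1.960 × √(2 × 0.5 × 0.5) + 1.282 × √(0.4 × 0.6 + 0.6 × 0.4)]² / 0.20² = (1.386 + 0.888)² / 0.04 ≈ 129.3, so 130 per arm and 260 in total. This matches the stated 260. For viral suppression, 25% v 45% with 130 per arm gives 92.7% power, against the stated 93%. The planned size therefore counts one participant per household, and members beyond the first are not needed for it.

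**2. Late members.** For a member enrolled after the household's allocation, the arm can be known with certainty, whatever the block size. The article gives no number of such members. Assumption: 5–10% of households add one. Then 260 × 0.05 = 13 and 260 × 0.10 = 26 participants.

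Illustration A, no true effect. First members link at 40% in both arms. Through selection, late members link at 60% in one arm and 20% in the other.
- 26 late members, 13 per arm: (52 + 7.8)/143 = 41.8% and (52 + 2.6)/143 = 38.2%, a false difference of 3.6 points.
- 13 late members, 6.5 per arm: (52 + 3.9)/136.5 = 41.0% and (52 + 1.3)/136.5 = 39.0%, a false difference of 1.9 points.

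Illustration B, upper case of 13 late members in the control arm. Half (6.5) refuse, and everyone else links at 40%, so the observed control rate is 40.0%.
- If no refuser would have linked, the full rate is (136.5 × 0.4)/143 = 38.2%. The error is 1.8 points, towards no difference.
- If all refusers would have linked, the full rate is (54.6 + 6.5)/143 = 42.7%. The error is 2.7 points, away from no difference.

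The direction is therefore open, and the size is about 2 to 4 points under these assumptions.

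**3. Blocks of 4.** Assume the nurse knows the block size and where blocks begin.

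*Own pack, all earlier assignments seen.* Best guess correct at positions 1 to 4: 1/2, 2/3, 2/3, 1. Mean = (0.500 + 0.667 + 0.667 + 1)/4 = 70.8%. Certain at positions 1 to 4: 0, 0, 1/3, 1. Mean = 33.3%.

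*One list shared at random by three nurses, each seeing only her own draws.* Each earlier slot is hers with probability 1/3. Having seen 0, 1, 2 or 3 earlier draws in the block, her best guess is right with probability 1/2, 2/3, 2/3 or 1, and the allocation is certain with probability 0, 0, 1/3 or 1.
- Correct, by position: 0.500, 0.556, 0.593, 0.630; mean 56.9%. A simulation of 200,000 blocks gave 57.0%.
- Certain, by position: 0, 0, 1/9 × 1/3 = 0.037, 6/27 × 1/3 + 1/27 = 0.111; mean 3.7%.

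The range is thus 57% to 71% correct, against 50% under full concealment.

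**The case against.** The strongest reply has four parts.

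*The article is condensed.* The order of consent and envelope opening, and whether nurses were told the block size, are procedures usually left to the full protocol. This stands, and their absence is not the point. The point is the interaction of two rules the article does state, the second visit and the inclusion of every eligible member, with the claim that extra members only add power. A member absent when the envelope is opened enrols afterwards whatever order is used for those present.

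*No breach is shown.* The list came from an independent statistician, the envelopes are sealed, and the nurse is called only when a test is positive, so she does not choose the order of households. Several criteria, such as age and previous treatment, are fixed facts. This also stands. Only eligibility judgement and consent could be influenced, and the higher predictability figure needs an own pack as well as knowledge of block size and boundaries. A reader might infer that nurses can foresee a third of allocations; the article does not support that as a fact.

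*Late members need not be hard to link.* A reader might equate people absent on a workday with the group the article describes as difficult to link. Subgroup analyses says this only of people working outside Lesotho for months at a time. Somebody away on a weekday and home at the weekend is not described there.

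*The number is unknown and probably small.* On the section's own inputs, taken per person and as independent, an absent adult found later would be enrolled with probability 0.94 × 0.05 × 0.90 = 4.2%. Couples may cluster, but no figure is given. The 5–10% above is an assumption only.

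**Conclusion.** The point holds as a risk that can be reduced cheaply. The stated rules allow some participants to be judged eligible and to consent after their household's arm is known, and the article treats these members as pure gain. Allocation at the first positive member's enrolment is the natural reading of same-day services by arm, although no sentence says so. The effect on linkage would probably be small, about 2 to 4 points under assumed late entry in 5–10% of households and strong selection, against a planned 20.

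The block-size issue is secondary: 57% to 71% correct guesses if nurses know block size and boundaries, with no statement of which arrangement applies.

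Two stronger conclusions are not supported. The documents do not show that bias occurred, or in which direction. Nor do they require late members to leave the primary analysis: that would reverse the explicit rule that all eligible members are included and would drop people whom the weekend visit is meant to reach. Sample size and power are unaffected.

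**What to change.** - Complete eligibility assessment and consent for every member present before opening the household's envelope.
- Record for each participant whether enrolment came before or after the household was allocated.
- Pre-specify a sensitivity analysis of both primary outcomes limited to participants who consented before allocation, and report late enrolment and refusal by arm. If the first step is followed, each enrolled household keeps at least one such participant, so this analysis retains the planned 130 per arm.
- Amend the sentence on power to say that additional members may add power but can also bring selection if they enrol after allocation.
- If recruitment continues, issue unused envelopes from a list with randomly varied block sizes that are not disclosed to the nurses.

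Late members stay in their household's arm and in the intention-to-treat analysis. The cost is one extra item on the enrolment form, one additional analysis and a new list for unused envelopes. Trial status gives a start on 22 February 2016 and an expected end of recruitment in May 2016, with possible extension. The changes to consent order and blocks therefore help only while enrolment is open. The flag and the sensitivity analysis can still be specified until the data are analysed, provided enrolment dates allow the flag to be reconstructed.
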